### Patient population

Patients who are due to undergo surgery for suspected liver tumour (primary or secondary). A sample size of up to 200 participants will be recruited from HHFT.

### Inclusion criteria

Male or female 18 years of age and older willing and able to give informed consent to participate in the study.Patients being considered for liver resection for primary or secondary liver cancer.

### Exclusion criteria

The participant may not enter the study with any known contraindication to MRI (including but not limited to pregnancy, a pacemaker or other metallic unfixed implanted device, metallic fragments, extensive tattoos, severe claustrophobia).Any other cause, including a significant underlying disease or disorder which, in the opinion of the investigator, may put the participant at risk by participating in the study or limit the participant’s ability to participate.

## Study assessments and data collection

Study visits are summarised in figure 1.

**Figure 1 F1:**
[figure not shown]
Study flow chart. Participants with informed consent will undergo pretreatment measurements at study visit 1 including height and weight, blood pressure, an online questionnaire, a non-contrast MRI scan and standard liver blood tests. Standard-of-care treatment will be followed and a blood sample and a sample tumour tissue explant will be collected. Twelve months following recruitment, a post-treatment telephone interview will occur as study visit 2. BMI, body mass index.

### Clinical assessment

Minimal medical history data will be collected including information regarding previous diagnosis of liver cancer, cirrhosis and comorbidities including chronic kidney disease and diabetes. Information about alcohol consumption, smoking and coffee intake will be collected. Information about any recent chemotherapy regimens will be collected.

### Blood tests

A blood sample will be collected as per routine clinical care, and blood results will be noted regarding biochemistry, renal profile, liver function tests, haematology, clotting, tumour markers including carcinoembryonic antigen, alpha-fetoprotein and CA19-9.

### Magnetic resonance imaging

Current routine clinical practice requests patients to visit the hospital 3 days prior to the planned surgery date for a COVID-19 test. At this visit, participants will be invited for an abdominal non-contrast enhanced MRI scan. Images will be processed to generate metrics indicating the liver tissue characteristics (Liver*MultiScan*) and future liver remnant volume (Hepatica) as previously described.^12^

### Impact of imaging on treatment decision-making

The clinical utility of quantitative MRI will be assessed through a survey of the consultant surgeons. The surgical plan prior to and after viewing the quantitative imaging reports will be noted, along with an indication as to the reason for any change in surgical plan with an expectation as to the impact on patient outcome:

Improved health of residual liver.Probability of postoperative complications.Shorter recovery time.

### Tissue sample collection

During the surgical resection operation, a sample of tumour tissue from the explant will be stored in two manners: fresh frozen and formalin fixed/paraffin embedded. This tissue and a blood sample will be stored locally and then transported for tissue processing and WGS by an approved vendor.

### Whole genome sequencing

Genetic information from tumour tissue and from participant blood sample will be examined. A case review of all participants will be performed with these data to evaluate the clinically actionable information and what steps would have been taken by the clinical care team if this information were available prior to the operation.

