#### Secondary objectives

To determine the utility of quantitative multiparametric MRI with Liver*MultiScan* to aid clinical decision-making in patients referred for liver resection.To compare computationally derived digital pathology results with human pathologist assessments of the tumour and non-tumour tissues.To compare the histopathological assessments of liver fat and fibro-inflammation with quantitative MRI metrics (cT1, proton density fat fraction (PDFF)).To evaluate the long-term outcomes and recurrence rates and recurrence patterns of patients as it relates to imaging and WGS.To evaluate whether WGS enables better stratification of patients prior to surgery.

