#### Primary endpoint

Proportion of patients for whom clinically actionable data are provided by WGS at the time of surgery. This will be evaluated retrospectively, with clinically actionable data defined as data which would result in a clinician choosing a different medical intervention to the current standard of care.

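### The primary WGS endpoint is a retrospective counterfactual with no described patient-level plan recorded before the result is opened, and explant-based WGS cannot show pre-operative utility in this pathway

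*Protocol article*

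**What the plan says.** All references are to the Protocol article.

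- **Primary endpoint.** The quantity is "Proportion of patients for whom clinically actionable data are provided by WGS at the time of surgery". It is assessed after the event, with "clinically actionable data defined as data which would result in a clinician choosing a different medical intervention to the current standard of care".
- **Whole genome sequencing.** Tumour and blood data are examined together in a case review of all participants, which considers "what steps would have been taken by the clinical care team if this information were available prior to the operation".
- **Tissue sample collection.** The tumour material is obtained at surgery: "During the surgical resection operation, a sample of tumour tissue from the explant will be stored in two manners". It is kept locally with a blood sample, and both later go to a vendor for sequencing.
- **Statistical analysis plan.** The variable analysed is binary: whether the intended management changed once WGS results were known. The section gives 25% as the change-in-management figure, 31% as the prevalence of actionable biomarkers, and 200 as the sample size.
- **Impact of imaging on treatment decision-making.** For MRI, a secondary endpoint, "The surgical plan prior to and after viewing the quantitative imaging reports will be noted", together with the reason for any change.
- **Secondary objectives.** One objective is "To evaluate whether WGS enables better stratification of patients prior to surgery".

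**The concern.** Two features of the primary endpoint limit what it can show.

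First, a change needs a starting point. The analysis section treats the endpoint as a change in what was intended for the patient, but the only baseline named is a general standard of care. For MRI the article describes a plan noted before and after the report. For WGS, which carries the primary endpoint, it describes a single judgement made with the result in hand. Such a judgement is open to hindsight: once a variant is known, it is easy to believe that one would have acted on it.

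Second, the review imagines that the information was available before the operation, yet the tumour material is obtained at that operation. Findings from blood and from tumour, and decisions before and after surgery, all enter one proportion. A reader could take that figure as evidence that WGS helps choose or plan surgery, or that it meets the pre-surgical stratification objective. In the pathway described, tumour WGS cannot show either.

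**Working it through.** **Step 1. The time point, side by side.**

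| Section | When the WGS information counts |
|---|---|
| Primary endpoint | At the time of surgery |
| Whole genome sequencing | Supposed to be available before the operation |
| Statistical analysis plan | Intended management after the WGS results |
| Tissue sample collection | Tumour obtained during the operation, then stored and shipped |

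The first three rows do not describe the same decision. Under the fourth, no tumour result can exist before or at surgery. Blood is stored and sent with the tissue, so the article does not show a germline result being available before surgery either, although nothing in it rules that out in principle.

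**Step 2. The baseline, side by side.**

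| | MRI (secondary) | WGS (primary) |
|---|---|---|
| Plan noted before the report | Yes | Not described |
| Plan noted after the report | Yes | Hypothetical steps, judged retrospectively |
| Reason for change noted | Yes | Not described |
| Comparator | The surgeon's own earlier plan | Standard of care in general |

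The operation performed is fixed before any tumour result exists, so part of the baseline is known. What is not described is a record, made before the WGS report is opened, of the rest of the intended management, such as post-operative treatment.

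**Step 3. The plan's own figure.** The article gives a sample of 200 for a 5% margin and a 95% CI. From n = z²p(1−p)/d²:

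- p = 0.25: 1.96² × 0.25 × 0.75 / 0.05² = 288.1, so 289.
- p = 0.31: 1.96² × 0.31 × 0.69 / 0.05² = 328.7, so 329.

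The stated 200 is not reproduced. That is a separate matter and neither supports nor weakens this point. What is needed here is the precision at 200:

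- Half-width at p = 0.25: 1.96 × √(0.25 × 0.75 / 200) = 0.060, or 6.0 points.

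**Step 4. Illustration of possible bias.** The documents give no misclassification rate, so f below is an assumption. The base is the 25% change-in-management figure. The 31% is a biomarker prevalence, which is a different quantity. If a fraction f of patients with no true change are judged to have changed, the observed proportion is p + (1−p)f:

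- f = 0.05: 0.25 + 0.75 × 0.05 = 0.2875 (28.8%), a shift of 3.75 points.
- f = 0.10: 0.25 + 0.75 × 0.10 = 0.325 (32.5%), a shift of 7.5 points.
- The shift equals the half-width when 0.75f = 0.060, so f = 0.080.

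At 5% the bias lies within sampling error; above about 8% it exceeds it. A larger sample would not reduce it.

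**Step 5. The opposite error.** If a fraction m of true changes is missed, the proportion falls by 0.25m. The 5% scenario is cancelled when 0.25m = 0.0375, so m = 15%. The net direction is therefore not settled by arithmetic.

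**The case against.** The strongest defence is that the counterfactual is open and deliberate. The study is observational, the endpoint is declared retrospective, and the review question is openly conditional. The primary objective concerns decision-making in patients referred for resection and is not limited to decisions before surgery; only a secondary objective is. Standard of care is named as the comparator, and Figure 1 says that it is followed. The surgical plan noted around the MRI report may itself precede WGS, since the scan is offered at a visit 3 days before planned surgery, although the article does not say when the surgeons' survey is completed. Review forms, masking and actionability rules may sit in the full protocol.

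Much of this stands, and it rules out three stronger readings that a reader might infer:

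- **That utility is overstated.** Upward bias is plausible, but the documents neither prove nor quantify it. A question framed on the operation could also miss post-operative uses of WGS and so understate overall utility.
- **That there is no baseline at all.** Standard of care is named, and the operation is fixed before tumour WGS exists.
- **That the assessors will know recovery or recurrence.** The article gives neither the date of the review nor what the assessors may see, and its silence on masking is not a fault in a condensed article.

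The defence does not remove the three wordings of the time point, the pooling of tumour and blood findings, or the fact that the tumour is sampled at the operation. A general standard is also not a recorded plan for a given patient, which is what a change in intended management needs.

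**Conclusion.** The point holds in a limited form. The primary proportion rests on a retrospective judgement without a described patient-level baseline, and is therefore open to hindsight bias. The time point is worded inconsistently. A proportion that pools explant and blood findings cannot show pre-operative utility, or support the pre-surgical stratification objective, in this pathway.

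The size of any bias is unknown. The 28.8 to 32.5% range assumes a true 25%, false credit in 5 to 10% of the remaining patients and no missed changes. It shows only that moderate misjudgement could match or exceed the 6.0-point sampling half-width. The conclusion on timing needs no such assumption; it follows from where the tumour tissue comes from. This is a worthwhile and cheap improvement. It does not invalidate the study.

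**What to change.** 1. **Two-step record within the planned case review.** Present the pre-operative information, with operative outcome, recovery and recurrence fields withheld, and record the intended management. Then open the WGS report and record it again. Count only a difference between the two records. This reduces hindsight but does not remove it if the reviewers treated the patient. Where feasible, therefore, record the intended management, including post-operative treatment, before the WGS result is returned.
2. **Tag each change** by source (germline or tumour) and by the decision affected (before or after surgery). Report the primary proportion overall and split that way.
3. **Align the time point** in the Primary endpoint, Whole genome sequencing and Statistical analysis plan sections, and describe any pre-operative utility from explant WGS as hypothetical.

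The cost is a slightly longer review form and, for step 1, hiding some fields at review. No new samples or study visits are needed. The headline proportion may be lower.

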### Digital pathology

Tissue explant samples will be analysed by the clinical histopathologist, and relevant information will be noted. Glass slides will be scanned and analysed using digital pathology methods to evaluate the objective scores of fibrosis, inflammation, ballooning and steatosis.

### Safety outcomes

No serious adverse events are anticipated as this study has been designed with minimal risks in mind, especially given the reduced healthcare capacity to deal with adverse events.

### Incidental findings

Any incidental findings will be reviewed by a radiologist and assessed by the clinical study team. If any structural organ abnormalities are found in the MRI scan or blood tests, a follow-up/note will be added to the participant’s medical record as this may have implications for the participant. The participant can seek counselling/support for any potential abnormal findings from their primary healthcare provider should they wish to.

The chief investigator and/or principal investigator(s) will subsequently be pleased to discuss the medical findings directly with the primary healthcare provider, if requested.

### Statistical analysis plan

The data will be evaluated to address the primary endpoint to calculate the proportion of patients in which the results from WGS would have resulted in a change in clinical management. The change in intended management after WGS results will be modelled as a binary variable on the basis of a binomial distribution.

From the literature, we estimate a prevalence of actionable biomarkers derived from genetics of 31%. Using a 5% allowable margin of error and 95% CI, a sample of 200 is required to give a reliable sample to achieve a change in management of 25% of patients.

Descriptive statistics will be reported for all endpoints specified and any interim analyses. Normality of the data will be determined by use of the Shapiro-Wilk test and visual study of histograms. Results will be expressed as mean with SD for continuous normally distributed variables, as median and IQR for non-normally distributed data and as counts and/or percentages for categorical variables. Linearity of continuous data will be assessed by scatter plots. To explore any potential systematic biases, categorical and demographic characteristics expressed as number (%) will be compared using χ^2^. For all tests, a p<0.05 will indicate statistical significance.

Correlations between results from Liver*MultiScan*/Hepatica-derived quantitative MRI metrics and histological features, as well as results from Liver*MultiScan* and genomic features will be determined with Spearman’s rank correlation coefficient and diagnostic performance will be assessed by the calculation of the receiver operating characteristic curve and the determination of the area under the receiver operating characteristic curve with 95% CIs. For all tests, a p<0.05 will be taken to indicate statistical significance.

To explore the impact of genetic variants associated with liver disease, the liver MR-derived biomarkers in those with and without known genetic variants associated with liver disease will be compared using a paired t-test (or non-parametric alternative).

Radiogenomic exploratory analysis will also be conducted to examine the correlations between image-derived biomarkers, genetic markers of organ damage or tumour malignancy. Digital pathology and circulation blood-derived biomarkers of the disease will be explored with Spearman’s r (rs), with pairwise comparison conducted using two-sided Kolmogorov-Smirnov tests. Listwise deletion will be employed per analysis to included data sets with complete cases for all parameters in the model.

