## Introduction

The incidence of treatable liver tumours is on the rise globally, driven by obesity, viral hepatitis and metastases from colorectal cancers. Survival rates can be improved with optimised allocation of treatment options including surgical resection, radiofrequency ablation, embolisation, chemotherapy and targeted molecular therapies (including immunotherapy). The key motivation of this study is to help patients access the most suitable treatment combinations by integrating radiogenomic^1^ and clinical data.

A similar integrated approach, integrating radiology and pathology, has been shown to improve outcomes in breast cancer care.^2^ Detailed pathological analysis of the surgical specimen from breast carcinoma biopsy provides valuable feedback to the radiologist, establishes the completeness of surgical intervention and generates predictive information for therapeutic decisions.^3^

Whole genome sequencing (WGS) has revealed cancer driver mutations and the complex molecular profile of liver cancer.^4^ In many metastatic solid tumours, WGS has been used to identify a significant patient population (31%) who present with a biomarker that predicts sensitivity to a drug and lack any known resistance biomarkers for the same drug.^5^ Identifying which patients possess genomic variants that predict drug response or resistance will allow clinicians to make the optimal treatment decisions. The next technological challenge is integrating WGS into scalable clinical practice.

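### A sample of 200 does not give a 5-point margin with a 95% CI: the plan's own inputs need 289 to 329, and 200 gives 6.0 to 6.4 points

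*Protocol article*

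**What the plan says.** The Statistical analysis plan section of the protocol article treats the primary endpoint, change in intended management after whole genome sequencing, as a single proportion "modelled as a binary variable on the basis of a binomial distribution". It starts from the literature: "we estimate a prevalence of actionable biomarkers derived from genetics of 31" per cent. It then concludes: "Using a 5% allowable margin of error and 95% CI, a sample of 200 is required to give a reliable sample", and ends the sentence with "to achieve a change in management of 25% of patients".

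Three other places bear on this:

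- **Primary endpoint.** Data count as clinically actionable only if they would lead a clinician to choose a different intervention from standard care. Being actionable and changing management are therefore the same event.
- **Introduction.** This shows where the 31% comes from. Sequencing of metastatic solid tumours was used to "identify a significant patient population (31%) who present with a biomarker that predicts sensitivity to a drug", with no known resistance biomarker for that drug.
- **Patient population.** Here 200 is a maximum: "A sample size of up to 200 participants will be recruited from HHFT".

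**The concern.** The sentence gives everything needed to check it: one binomial proportion, a margin, a confidence level and two candidate proportions. Those inputs do not lead to 200 with either proportion.

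This is the article's only justification for the study size, and it concerns the primary estimate. A reader would expect a 95% interval about 10 points wide. The study would give one of 12 to 13 points, and a wider one if fewer than 200 participants are evaluable.

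Two further features make the statement hard to repair by guesswork. First, it does not say whether 31% or 25% is the planning value. The article's own definition makes actionable data and changed management one quantity, yet the paragraph gives each its own figure. Second, a sample size cannot achieve a 25% rate of changed management. It can only estimate that rate with some precision, or test it against a reference value, and no reference value is stated.

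**Working it through.** **Inputs, all from the Statistical analysis plan section**

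- Margin (half-width) d = 0.05 and a 95% interval: "5% allowable margin of error and 95% CI". No one-sided bound is mentioned, so z = 1.96 and z² = 3.8416.
- Candidate proportions p = 0.31 and p = 0.25.
- Stated result: n = 200.

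**Step 1. Try to reproduce 200.** For a single proportion, n = z² p(1 − p) / d².

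- p = 0.25: 3.8416 × 0.1875 / 0.0025 = 288.1, so 289.
- p = 0.31: 3.8416 × 0.2139 / 0.0025 = 328.7, so 329.

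The stated figure falls short by 89 and 129 respectively. The choice of interval does not rescue it: the Wilson interval needs 286 and 326, and the exact (Clopper-Pearson) interval 306 and 347.

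**Step 2. What 200 delivers.** Half-width = 1.96 × √(p(1 − p)/n).

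| p | Half-width at n = 200 | 95% interval (normal) | 95% interval (exact) |
|---|---|---|---|
| 0.25 | 1.96 × √(0.1875/200) = 0.060 | 19.0% to 31.0% | 19.2% to 31.6% (50/200) |
| 0.31 | 1.96 × √(0.2139/200) = 0.064 | 24.6% to 37.4% | 24.7% to 37.9% (62/200) |

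Put the other way, an interval of ±5 points at n = 200 has about 90% confidence at p = 0.25 and 87% at p = 0.31.

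**Step 3. Look for any reading that gives 200.**

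| Change to the stated inputs | n | Conflict with the text |
|---|---|---|
| 90% interval (z = 1.645), p = 0.25 | 203 | Text says 95% |
| 90% interval, p = 0.31 | 232 | Text says 95%, and it misses |
| Margin of 6 points, p = 0.25 | 3.8416 × 0.1875 / 0.0036 = 200.1 | Text says 5% |
| Margin of 6 points, p = 0.31 | 229 | Text says 5%, and it misses |
| Continuity correction, p = 0.25 / 0.31 | 308 / 349 | Misses |
| 5 points as the full width, p = 0.25 / 0.31 | 1153 / 1315 | Misses |
| One-sample test between 25% and 31%, 80% to 90% power | 338 to 594 | No test or power stated, and it misses |

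Solving for the proportion at n = 200, d = 0.05 and 95% gives p(1 − p) = 200 × 0.0025 / 3.8416 = 0.130, so p is about 0.154. That value appears nowhere in the article. A finite population correction would need a source population of about 509 (p = 0.31) or 652 (p = 0.25), and none is stated.

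The closest match is 25% ± 6 points, where 6 is also 31 minus 25. The 200 may have come from that, with the margin then reported as 5%. This is an inference; the article does not say so.

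**Step 4. Fewer than 200 evaluable.** Eligibility requires only that resection is being considered, whereas tumour tissue for sequencing is taken at the operation, so some participants may have no result. If 160 were evaluable (an assumption, for illustration), the half-width at 31% would be 1.96 × √(0.2139/160) = 0.072, or 7.2 points.

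**The case against.** The strongest reply is that the number of participants may be right and only the margin misreported. The 6-point reading reproduces 200 almost exactly, so describing the study as short by 89 to 129 participants would mislead. The loss of precision is 1.0 point at 25% and 1.4 points at 31%. The study is a single-group observational cohort with a descriptive primary proportion, and no test, threshold or treatment allocation depends on ±5 points.

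Much of this stands. It supports correcting the stated precision over enlarging the study. It does not rescue the sentence, because a 5% margin with a 95% interval is what the article promises and 200 does not deliver it.

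It can also be said that 31% and 25% are different quantities, since some patients with a biomarker would not have their management changed. That is coherent if 31% is the rate of drug-sensitivity biomarkers. But then 31% belongs to the last secondary endpoint, and the paragraph should not present it as the rate of actionable findings behind the primary one. The narrower criticism remains: the planning value is not identified.

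Finally, a recruitment ceiling set at the calculated target is ordinary practice. The wording matters here only because a maximum of 200 leaves no room for participants without a result if 200 evaluable are really required.

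**Conclusion.** The sample size statement is wrong as written. On its own inputs the requirement is 289 (at 25%) to 329 (at 31%). With 200 evaluable participants the 95% half-width is 6.0 to 6.4 points, not 5. This rests on a two-sided 95% interval, a margin meaning half-width, and one binomial proportion, which is the ordinary reading of the text. The conclusion is the same with Wilson or exact intervals.

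Which input slipped cannot be settled from the article. The practical loss is modest and does not threaten the study, but the precision claimed for the primary estimate has to be corrected, and the planning proportion has to be made clear.

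**What to change.** Keep the planned size and rewrite the paragraph:

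1. Replace the precision claim with: *With 200 evaluable participants, the half-width of the 95% confidence interval is 6.4 percentage points if the proportion is 31% and 6.0 if it is 25%.* If fewer are expected to be evaluable, add that case (for example 7.2 points at 31% with 160, labelled as an assumption).
2. Drop the wording about achieving a 25% change in management. State one planning proportion for the primary endpoint as the Primary endpoint section defines it.
3. Attach the 31% to the drug-sensitivity biomarker endpoint, where it belongs.
4. Say whether 200 means recruited or evaluable participants, so that the requirement and the recruitment ceiling agree.
5. Preferably, name a Wilson or exact interval for the primary proportion.

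The cost is the rewording of one paragraph and a slightly less favourable stated precision. No extra participants are needed. If the sponsor does want ±5 points at 95%, the alternative is 289 to 329 evaluable participants, depending on the planning value.

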**Trial registration number:**

NCT04597710

Strengths and limitations of this studyPrecision1 will be the first study examining the clinical utility of radiogenomic information during the surgical treatment planning stage for patients with primary and secondary liver cancer.Our prospective study is designed to allow us to understand the extent to which quantitative MRI of the liver impacts surgical treatment planning.The additional value of whole genome sequencing will be evaluated to help us identify the presence of any clinically actionable genetic biomarkers which may support precision medicine provision to patients.All patients being considered for liver resection may be eligible for the study, regardless of tumour type or clinical background.The primary limitation of this study is the omission of a tightly matched negative control group where the impact of quantitative imaging on improving patient outcomes could be rigorously examined.

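### The MRI–genomic Spearman correlations are not stratified by tumour type, so differences between cancer types may appear as radiogenomic associations

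*Protocol article*

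**What the plan says.** **Method.** The Statistical analysis plan section of the protocol article says that correlations between LiverMultiScan results and "genomic features will be determined with Spearman’s rank correlation coefficient". It adds: "For all tests, a p<0.05 will be taken to indicate statistical significance". An ordinary Spearman coefficient takes no covariate.

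**Cohort.** The inclusion criterion is "Patients being considered for liver resection for primary or secondary liver cancer". The strengths and limitations list goes further: "All patients being considered for liver resection may be eligible for the study, regardless of tumour type or clinical background".

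**The two variables.** The Introduction describes LiverMultiScan as measuring liver tissue characteristics such as fat and fibro-inflammation. The Whole genome sequencing section takes genetic data from both tumour tissue and blood, so genomic features include somatic and germline variants.

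**Tumour type in the analysis.** No section names it as a stratum, subgroup or covariate. The χ² comparison meant to look for systematic bias does not name its groups and is not tied to the correlations. The missing-data sentence mentions a model but lists no covariates.

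**The concern.** MRI metrics describe the background liver, and a somatic feature describes the tumour. If both differ between, say, primary cancers and metastases, a coefficient calculated across everyone picks up that difference even when the two are unrelated among patients with the same kind of cancer. The significant result then says little more than which cancer the patient has, and histology already shows that.

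The article gives some reason to expect a difference in background liver. It describes the rise in liver tumours as "driven by obesity, viral hepatitis and metastases from colorectal cancers", which places causes of chronic liver disease beside metastatic spread from elsewhere.

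What is at stake is how the MRI–genomic associations are read. The Introduction wants genetic variants linked to radiological features for use in clinical software, and a marker that only separates tumour types would add little there. A multiplicity correction would not help, because the pooled association is real in the mixed population and is only open to misreading.

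**Working it through.** **1. The plan's own figure.** The article gives no power or precision figure for these correlations. Its sample size belongs to the primary proportion: "a sample of 200 is required to give a reliable sample to achieve a change in management of 25% of patients". For that proportion, estimated to within 5 points either side at 95% confidence, the usual formula gives 1.96² × 0.25 × 0.75 / 0.05² = 288.1, so 289, not 200. That is a separate matter on which this point does not depend. Here 200 is used only as the number analysed.

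**2. Inputs.**

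| Input | Value | Source |
|---|---|---|
| n | 200 | Statistical analysis plan section (elsewhere up to 200) |
| Significance level | 0.05 | Same section; two-sided assumed |
| Share of primary tumours, s | 20%, 35%, 50% | Assumed |
| Difference in MRI metric between types, d | 0.3, 0.5, 0.8 SD | Assumed |
| Feature frequency, primary (a) vs secondary (b) | 30% vs 10%; 50% vs 5% | Assumed |
| Association within each type | None | Set, to isolate the between-type effect |

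**3. Expected coefficient in the mixed cohort.** With unit variance within type, the correlation is approximately

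r = s(1−s)·d·(a−b) / √{[1 + s(1−s)d²]·p(1−p)}, where p = s·a + (1−s)·b.

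Central case (s = 0.35, d = 0.5, 50% vs 5%):
- p = 0.35×0.50 + 0.65×0.05 = 0.2075, so p(1−p) = 0.1644
- s(1−s) = 0.2275; numerator = 0.2275×0.5×0.45 = 0.0512
- 1 + 0.2275×0.25 = 1.0569; r = 0.0512/√(1.0569×0.1644) = 0.123
- r√199 = 1.73; chance of exceeding 1.96 = P(Z > 0.23) ≈ 41%

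Mildest case (s = 0.20, d = 0.3, 30% vs 10%):
- p = 0.14, p(1−p) = 0.1204; numerator = 0.16×0.3×0.20 = 0.0096
- r = 0.0096/√(1.0144×0.1204) = 0.027; r√199 = 0.39; rejection ≈ 7%, counting both tails

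If d = 0 or a = b, the numerator is zero and so is r. Both variables must differ by type.

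**4. Simulation.** Each setting had 2,000 trials. Pooled Spearman was compared with a van Elteren-type test. That test ranks the MRI metric within each tumour type, divides the centred ranks by (stratum size + 1), sums their products with the centred feature over strata, and divides by the stratified standard error.

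| Setting (n=200, no within-type association) | Pooled Spearman p<0.05 | Stratified |
|---|---|---|
| 35% primary, 0.5 SD, 50% vs 5% | 39–42% over repeated simulations | 5% |
| 20–50% primary, 0.3–0.8 SD, 50% vs 5% | about 14–77% | 4–6% |
| 20–50% primary, 0.3–0.8 SD, 30% vs 10% | about 7–26% | 4–6% |
| Only one of the two variables differs by type | 4–6% | 4–6% |

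**5. Other contrasts.** With 30% primary and a feature in 10% of primaries versus 60% of secondaries, the pooled rate was 30% at 0.5 SD and 60% at 0.8 SD. With 20% versus 40% it was 10% and 14%. With only 10% primary, these contrasts gave about 5–16%. The stratified rate was 4–6% in every setting.

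**The case against.** **The article is condensed.** It does not use the words pooled or unadjusted, and a full plan that is not shown may stratify. This stands as a caution, since the pooled reading is an inference. But the article does state its method, and that method, applied as written to the cohort as written, has no protection against this. The point is about the method stated and not about detail left out.

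**The marginal association may be what is wanted.** Spearman tests independence in the whole cohort, which is false in the simulated settings, so the rejection rates are not type I errors for that question. This is right. They show how often a significant coefficient would occur with nothing behind it within a cancer type. The choice is one of estimand, and both results can be reported.

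**Tumour type may not be a common cause.** A reader might infer that it is an established confounder. The documents do not show that. The Introduction lists obesity and viral hepatitis as drivers of tumours, which puts liver disease upstream of tumour type, so stratifying could remove part of a real pathway. This is why a labelled pooled coefficient should be kept.

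**Germline variants are less exposed.** This stands; the mechanism is clear only for tumour-derived features.

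**The numbers are assumed.** This stands too. The effect is small when the contrast is modest or the mix lopsided, so the supportable wording is that such associations may appear, not that they will.

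**Conclusion.** The point holds in conditional form. The stated method does not separate tumour types in a cohort that mixes them. If an MRI metric and a somatic feature both differ by type, significance without any within-type association may occur in about 7–26% of trials (30% versus 10% feature) or 14–77% (50% versus 5% feature), against 4–6% after stratification. These ranges rest on n=200, two tumour groups, a normally distributed MRI metric and the assumed mixes and contrasts above. None of those contrasts comes from the documents.

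Two wider readings are not supported:
- A reader might infer that the exploratory radiogenomic analysis has the same fixed method. The sentence planning to "examine the correlations between image-derived biomarkers, genetic markers of organ damage or tumour malignancy" names none; Spearman appears in the next sentence, for digital pathology and blood biomarkers.
- A reader might infer that WGS prediction of 1-year mortality and recurrence is confounded in the same way. No pooled coefficient is named for that endpoint, and a predictor that carries tumour-type information still predicts. Whether it adds to histology is a different question, not tested here.

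MRI–genomic correlation is neither the primary endpoint nor a listed secondary one. The consequence is for interpretation, and the change should be made on that ground.

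**What to change.** For the LiverMultiScan–genomic associations in the Statistical analysis plan section, state that interpretation rests on an analysis stratified by tumour group:

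- Form groups from the clinical histopathology of the explant (Digital pathology section): at least primary versus secondary, and finer where numbers allow.
- Use the van Elteren test for features that are present or absent, and a within-group (partial) Spearman coefficient for ordered or continuous features.
- Report any pooled coefficient beside the stratified result, labelled as unadjusted for tumour type.

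**Cost.** The change is to wording and analysis only. No new data should be needed, assuming the histopathology report identifies tumour type. The stratified analysis has less power for features that vary mainly between tumour types, and it does not describe the marginal association, which is why the pooled figure stays in the report.
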